### Participant timeline {13}

The participant timeline is shown in Fig. 3.

**Fig. 3 Fig3:**
[figure not shown]
Participant timeline

### Sample size {14}

The sample size calculation is based on previous studies reporting MALE rates in PAD patients after re-vascularization procedures. These studies were heterogeneous in study design, patient selection, techniques (proportion of patients with endovascular approach), and findings [13–24]. Hess et al. reported a MALE incidence of 10% at 12 months among 381,415 re-vascularized patients that were included in the Premier Healthcare Database between April 2009 and September 2014 [19]. In addition, there were two larger interventional studies reporting 30-day MALE incidence after surgical or endovascular therapy of symptomatic PAD patients. Fashandi et al. reported a MALE incidence of 3.2% in patients with claudication at 1 month following therapy [21]. Mehaffey et al. reported a MALE incidence of 12.2% in patients with critical limb ischemia (CLI) [22]. The COMPASS trial estimated a MALE incidence of 2.0% among 6.341 patients with PAD at 21 months, of which 35% were asymptomatic. The MALE incidence was 3.6% among the subgroup of patients with previous re-vascularization procedures [24]. A subgroup analysis of the Fourier trial estimated a MALE incidence of 1.5% among 3.642 patients with PAD (31% asymptomatic) at 12 months [23]. In the XTOSI study, the 6-month amputation-free survival was 90% in patients receiving sirolimus-coated balloon catheters.

Based on these studies, assuming a 10% event rate (MALE) within 12 months in both the control and intervention group, and a non-inferiority margin of 5% expressed as absolute risk difference, a total of 1132 patients (566 patients per treatment group) allow to show non-inferiority of the intervention group with a power of 80% and a type I error rate of *α* = 2.5% one-sided. Assuming a drop-out rate of 5%, including randomization failures, a total of 1200 patients will be randomized in the study.

### Recruitment {15}

The strategy for study recruitment is displayed in Fig. 4. The screening phase will be composed of two phases: (i) clinical screening and (ii) angiographic screening. Both phases will take place at the study centers and involve patients with peripheral arterial disease referred for evaluation of re-vascularization or direct referral for re-vascularization by study center physicians or other treating physicians, as per routine procedures.

**Fig. 4 Fig4:**
[figure not shown]
Study recruitment

The Clinic of Angiology of the University Hospital of Zurich and the Division of Angiology of the Cantonal Hospital Fribourg currently performs together approximately 1050 peripheral interventions per year. Therefore, assuming that more than 80% of the potentially eligible patients will be finally enrolled in the study, the patient recruitment is expected to last no longer than 30 months with the Last-Patient-Out visit for the 5-year cumulative mortality analysis planned in 2028.

## Assignment of interventions: allocation

### Sequence generation {16a}

After the angiographic screening and definition of the target lesion, but prior to any therapeutic intervention, each eligible patient will be assigned to one of the two open treatment arms of this trial by an online randomization tool. This generation of the randomization sequence was generated before the start of the study outside the platform, REDCap, serving for data collection and used other software (R). Randomization will be stratified according to the stage of disease, namely elective re-vascularization (Fontaine stages I–II) vs. critical rescue re-vascularization (Fontaine stages III–IV), and study center. A block randomization will be done using an online random tool (REDCap, Vanderbilt University, v9 1.0).

### Concealment mechanism {16b}

Allocation will be concealed and treatment will be done immediately thereafter during the same angiographic session.

### Implementation {16c}

The allocation sequence was generated using a statistical software by a data analyst from the Clinical Trial Center of the University of Zurich. Participants will be enrolled and assigned to the intervention by the study physicians and investigators from the two study sites.

## Assignment of interventions: blinding

### Who will be blinded {17a}

The trial is conducted as an open-label study.

### Procedure for unblinding if needed {17b}

The trial is conducted as an open-label study.

## Data collection and management

### Plans for assessment and collection of outcomes {18a}

#### Assessment of primary and secondary outcomes

For the primary analysis, the primary efficacy outcome will be assessed within 1 year from randomization. Formal visits are planned at hospital discharge, between days 30 and 180, and at 1 year (flowchart). The same applies for all the secondary and safety outcomes. This strategy will allow minimal burden for the patients, who will not undergo additional visits that are not part of routine clinical and sonographic follow-up at our center. In particular, given the “hard” nature of the primary efficacy outcome, the ease of assessment, and the fact that these patients are usually referred to the center where the intervention was performed, the risk of reporting bias would be minimal.

The relatives will be instructed to contact the study investigators in the presence of novel signs of symptoms or complications any time after enrolment. A 24/7 telephone number for emergencies is available.

#### Assessment of safety outcome

Survival status and the cause of death will be assessed during follow-up if a patient misses a scheduled visit or cannot be contacted telephonically, as well as at the end of clinical follow-up (year 1) and at the time of long-term follow-up (year 2 and year 5).

In the case a patient is not followed at the study centers, the treating physicians, the patient, and the relatives will be instructed to contact the study investigators if a severe adverse event is suspected. All patients will be instructed to return to the hospital as soon as new symptoms occur, at which time information about the time of onset, intensity, and duration of the event will be collected, and objective tests and clinical examination may be performed.

The Data Safety Monitoring committee is responsible for the oversight and safety monitoring of the study. Regular evaluations of safety data will be after inclusion of multiples of 150 patients. The committee advises the sponsor regarding the continuing safety of the trial subjects.

### Plans to promote participant retention and complete follow-up {18b}

In order to collect the data for the primary outcome, the patients will undergo a routine visit. If a patient will not undergo or will not be able to attend routine in-hospital visit, or if no information will be spontaneously obtained from the treating physicians between day 30 and day 180, the investigators will verify whether the patient has been recently admitted in another department of the study center, the investigator tries to contact the patient or the relatives by phone call. The phone interviews will be performed by specially trained staff of the University of Zürich and will be based on a standardized list of questions integrated in the eCRF.

This strategy will allow minimal burden for the patients, who will not undergo additional visits that are not part of routine follow-up. In particular, given the “hard” nature of the primary efficacy outcome, the ease of assessment, and the fact that these patients are usually referred to the center where the intervention was performed, the risk of reporting bias would be minimal. In order to limit the amount of missing data points, we have implemented a sequential system to optimize data collection: (i) Information will be collected at the time of the planned visit; (ii) telephone contacts of patients/relatives/treating physicians; (iii) education of patients to refer to the study center if any new symptoms occur; and (iv) assessment of online medical charts and “Zivilstand.”

### Data management {19}

For the data entry, the data management, as well as data storage and security, an Internet-based secure data base REDCap (Vanderbilt University, v9 1.0) developed in agreement to the Good Clinical Practice (GCP) guidelines provided by the Clinical Trials Center (CTC) Zurich will be used for this study. Data will be stored in an oracle data base, which will be installed on a local server at the University Hospital of Zurich and routine back-ups will be performed in order to prevent data loss.

The data entry via REDCap application occurs web-based and the data will be transferred encrypted. Each user will receive a personalized REDCap account. The possibly audit-trail information will be stored in the REDCap application for each data entry, data change, or data deletion including the time and name of the user. In addition, data entered into the eCRF will undergo automatic plausibility checks where possible. An overview for the implemented plausibility checks will be available for each version of the eCRF.

In order to promote data quality and detect possible errors at an early time, regular monitoring visits at the investigator’s site prior to the start and during the study will be performed. Also, the sponsor-investigator organizes additional professional independent monitoring for the study, collaborating also with the Clinical Trials Center of the University Hospital Zurich. Audits and inspections to guarantee and control quality data may be conducted by the Competent Authority or Competent Ethics Committee, respectively.

### Confidentiality {27}

Direct access to online source documents will be permitted for purposes of monitoring, audits, and inspections. The investigator-sponsor, all investigators, the members of the clinical event committee, the study coordinator, and the bio-statistician will have access to the investigation plan and data sets during and after the study. The bio-statistician will have access to the statistical code.

### Plans for collection, laboratory evaluation, and storage of biological specimens for genetic or molecular analysis in this trial/future use {33}

No biological specimens will be collected during the trial.

## Statistical methods

### Statistical methods for primary and secondary outcomes {20a}

In the primary analysis of this trial, the absolute risk difference for MALE at 12-month follow-up between treatment groups will be estimated, together with its 2-sided 95% confidence interval. The trial statistician will perform the analyses after termination of the trial. If the overall event rate estimated at interim analysis is > 10%, an unblinded estimation of the risk difference and confidence interval will be calculated. The confidence level *α* will then be spent such that the overall type I error is preserved for an interim analysis and a final analysis, using a Lan-DeMets spending function. At interim, the confidence level will therefore be 99.95% and for the final analysis, it will be 95.05%.

If the null hypothesis concerning the primary objective is rejected (and the primary objective, non-inferiority, is thus established), further confirmatory statistical tests on primary and secondary endpoints will be performed using a pre-specified hierarchical order based on the clinical importance of the considered outcomes:

1. Superiority for the composite of unplanned (major or minor) index-limb amputations or any target lesion re-vascularization within 365 days after enrolment (*α* = 2.5% one-sided)

2. Superiority for MALE within 365 days after enrolment (*α* = 2.5% one-sided)

No additional reduction or splitting of the single *α* levels is necessary for this reason since the predefined ordering avoids any choice in the assessment (Guideline on multiplicity issues in clinical trials, European Medicines Agency; EMA/CHMP/44762/2017).

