### Methods for additional analyses (e.g., subgroup analyses) {20b}

Multivariable logistic regression for the outcome MALE event will be used to estimate an adjusted treatment effect, given the stratification variables. The following subgroups are pre-specified for analysis of heterogeneity of effects: age ≥ 75 vs. < 75, men vs. women, patients with elective re-vascularization (Fontaine I–II) vs. critical re-vascularization (Fontaine > II), patients with 1 vs. more than 1 level intervention, de novo lesion vs. restenosis, total occlusion vs. partial occlusion, distal vs. proximal lesions. If there is evidence for a differential treatment effect within subgroups (i.e., *p*-value of interaction test < 0.05), the treatment effect will be reported within subgroups as odds ratios or hazard ratios for time-to-event outcomes.

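### The primary risk difference appears not to use the randomisation strata (Fontaine stage and centre), which would make its interval slightly too wide and the non-inferiority test slightly conservative

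*Protocol article*

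**What the plan says.** Four parts of the protocol article bear on this.

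- *Sequence generation {16a}*: "Randomization will be stratified according to the stage of disease" (Fontaine I–II against III–IV) and also by study centre.
- *Statistical methods for primary and secondary outcomes {20a}*: in the primary analysis, "the absolute risk difference for MALE at 12-month follow-up between treatment groups will be estimated, together with its 2-sided 95% confidence interval". No stratified or adjusted estimator is named, here or for the two superiority tests that follow in the hierarchy.
- *Methods for additional analyses {20b}*: "Multivariable logistic regression for the outcome MALE event will be used to estimate an adjusted treatment effect, given the stratification variables". This is the only analysis in the article that uses the stratification factors.
- *Sample size {14}*: the calculation rests on "assuming a 10% event rate (MALE) within 12 months in both the control and intervention group" and on "a non-inferiority margin of 5% expressed as absolute risk difference". It gives 566 patients per group for 80% power at 2.5% one-sided.

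The word unadjusted does not occur. That the primary analysis is unadjusted is inferred from {20a} and {20b} read together.

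**The concern.** Stratified randomisation makes the two arms nearly identical in their mix of disease stages. The difference in event proportions then no longer varies because of chance imbalance in stage. The usual two-sample standard error does not know this: it is built on p(1−p) for the pooled population and so still includes the variance between stages. If stage predicts the outcome, the interval is wider than it need be and the test rejects less often than its nominal level allows.

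The article gives reason to think that stage matters. Its sample-size section cites a MALE incidence of 3.2% in claudication and 12.2% in critical limb ischemia at 30 days. The trial is planned at 80% power with nothing in hand, so precision that costs nothing is worth having. A crude primary analysis beside an adjusted additional one also leaves room for argument if the two point different ways.

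**Working it through.** **Inputs from the article.** Overall 12-month rate 10% in both arms, margin 5 points, one-sided 2.5%, power 80%, 1:1 allocation, 566 per arm. Stage rate ratio 12.2/3.2 = 3.8125; these are 30-day figures from two different studies and are used only as a ratio.

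**Assumptions not in the article.** Share of patients in Fontaine III–IV: 30% to 70%. No effect of centre on the outcome.

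**Step 1: the planned sample size.** n = 2 × 0.10 × 0.90 × (1.960 + 0.842)² / 0.05² = 565.1, so 566 per arm and 1132 in total. The article's figure reproduces exactly with no stratification term.

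**Step 2: unadjusted precision.** SE_u = √(2 × 0.09/566) = 1.783 points, so the 95% half-width is 3.50 points. By the planning formula, power is Φ(5/1.783 − 1.960) = 80.1%.

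**Step 3: stratified precision.** With share w in Fontaine III–IV, the rate in Fontaine I–II is a = 0.10/((1−w) + 3.8125w), and in III–IV it is b = 3.8125a. The variance per patient becomes V = (1−w)a(1−a) + w·b(1−b), and SE_s = √(2V/566). Example with w = 0.3: a = 5.42%, b = 20.68%, V = 0.0359 + 0.0492 = 0.0851 against 0.09, so SE_s/SE_u = 0.9725.

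**Step 4: consequences.** With arms balanced on stage, SE_s is the true standard deviation of the estimate. Therefore:
- excess of the unadjusted SE = SE_u/SE_s − 1
- one-sided error of the unadjusted test = 1 − Φ(1.960 × SE_u/SE_s)
- power of the unadjusted test = Φ((5 − 1.960 × SE_u)/SE_s), SEs in points
- power of the stratified test = Φ(5/SE_s − 1.960)
- n per arm needed if stratified = 2V × (1.960 + 0.842)²/0.05²

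| Share III–IV | Rates I–II / III–IV | SE too large by | Half-width if stratified | One-sided error, unadjusted | Power, unadjusted / stratified | n per arm if stratified |
|---|---|---|---|---|---|---|
| 30% | 5.42% / 20.68% | 2.8% | 3.40 points | 2.2% | 80.7% / 82.2% | 535 |
| 50% | 4.16% / 15.84% | 2.0% | 3.43 points | 2.3% | 80.5% / 81.6% | 544 |
| 70% | 3.37% / 12.84% | 1.1% | 3.46 points | 2.4% | 80.3% / 80.9% | 554 |

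In patients, the loss is 2 × (566 − 554) = 24 to 2 × (566 − 535) = 62 in total.

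**Step 5: simulation** (200,000 trials per setting, arms balanced within stage, 50% in III–IV, rates 4.16% and 15.84%). The mean unadjusted SE was 1.780 points, the true standard deviation 1.751 and the mean stratified SE 1.745. Power was 80.6% unadjusted and 81.6% stratified. With the true difference at the margin, non-inferiority was declared in 2.3% of trials unadjusted and 2.6% with a stratified Wald interval. At 30% in III–IV the last two figures were 2.1% and 2.5%.

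**Step 6: sensitivity to the rate ratio.** At an assumed ratio of 2, the SE is 0.4% to 0.7% too large. At an assumed ratio of 8 it is 1.7% to 6.5% too large; the top of that range (30% in III–IV) gives stratified power of 84.8% and 498 per arm.

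**The case against.** **It rests on an inference.** The article names no estimator or interval method for the risk difference. Such detail is often left to the statistical analysis plan, which is not shown and may specify a stratified analysis. This stands as a limit on certainty. It does not remove the point: the article does take up adjustment, names the model and the factors, and files it apart from the primary analysis. A sample size that reproduces without stratification fits the same reading, though that alone would prove little.

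**The harm is small and on the safe side.** This also stands. The unadjusted test makes a false claim of non-inferiority less likely, and the planned 80% power is still reached. A reader might infer that the trial is underpowered or its error rate uncontrolled; neither follows.

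**Larger losses.** A reader might arrive at an SE about 10% too large and some 225 patients lost. That needs, for example, 30% critical ischemia with rates of 2% and 28.7%, where V/0.09 = 0.834 and 1132 × (1/0.834 − 1) = 225. The implied rate ratio is about 14, against 3.8 in the article. It also sets a 12-month claudicant risk below the cited one-month 3.2%. The gradient could exceed 3.8, because re-vascularisation counts in the primary outcome only when done for critical limb ischemia, but the article does not quantify this.

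**The odds-ratio reading.** A reader might infer that the adjusted analysis cannot be set against the margin because it yields an odds ratio. A raw odds ratio indeed has no fixed counterpart: 5 points correspond to 1.59 at a 10% control rate, 2.11 at 5% and 1.42 at 15%. But the article names odds ratios only for subgroup effects ("the treatment effect will be reported within subgroups as odds ratios or hazard ratios for time-to-event outcomes") and gives no scale for the overall adjusted effect. The same model can also yield a standardised risk difference.

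**Conclusion.** The point holds as a modest loss of efficiency. On the natural reading of the article, the primary interval is about 1% to 3% too wide and the test runs at about 2.2% to 2.4% one-sided. Using the strata would raise power from about 80–81% to 81–82%, worth about 24 to 62 patients. These figures assume a 10% overall rate, a stage rate ratio of 3.8 carried from 30 days to 12 months, 30% to 70% in Fontaine III–IV and no effect of centre. Losses up to about 6.5% in the SE require a ratio of 8, which the article does not supply. The sample size is correct for the unadjusted analysis, and type I error is not inflated. The change is worth making because it is free and brings the analysis into line with the randomisation.

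**What to change.** In {20a}, define the primary estimate as a risk difference stratified by Fontaine stage and centre (Mantel-Haenszel weights with a stratified interval), or as the standardised risk difference from the logistic model already planned in {20b}. Test it against the 5-point margin. A stratified score interval is preferable to a Wald one, since the stratified Wald interval came out marginally above 2.5% in one simulated setting. Use the same stratification for both superiority tests, and keep the unadjusted difference as a sensitivity analysis. If the analysis plan already says this, one sentence in the protocol settles the matter.

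The cost is wording only: both factors are recorded at randomisation, and no extra data or patients are needed. The change should be fixed before any unblinded interim estimate of the risk difference.

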### Interim analyses {21b}

A single interim analysis with information rate of 50%, i.e., 300 patients per arm, 600 in total, is planned. If at interim the overall event rate exceeds a pre-specified threshold of 10%, the event rate will be estimated in both treatment groups (unblinded).

Following D’Agostino et al. [25] “for efficacy reasons one can argue that there is no real ethical issue with seeing the [non-inferiority] trial to completion from an efficacy perspective”. However, “interim analyses are also important in a non-inferiority trial for safety reasons, either to ensure the experimental treatment is not doing more harm than good (R1), or that it is superior with regard to specific adverse events (R2).”

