#### Monitoring for safety

Safety concerns in this study are twofold: (R1) the efficacy endpoint (MALE) may differ substantially between treatment groups and (R2) mortality may differ between treatment groups. On safety grounds, termination of the trial may be recommended after the interim analysis. However, such assessments may potentially have implications for falsely concluding that there is an adverse effect. No statistical reasons for stopping the trial at interim analysis are declared.

Notation:

*δ*_Int_: between-group risk difference *p*_exp_ − *p*_con_ at 12 months at interim analysis for MALE

*d*_Int_: between-group risk difference *π*_exp_ − *π*_con_ at 12 months at interim analysis for mortality

exp = experimental group, coated devices

con = active control group, uncoated devices

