**Table Tabb:** 

Scenario	Reasoning	Interpretation	Action
Interim analysis after 600 patients followed up 12 months (50% of total sample size)			
*p*_total_ ≤ 0.10	Verify assumptions about nuisance parameters	Obtain an estimate of overall MALE event rate at interim. Assumptions about nuisance parameters seem to be realistic.	Continue trial without any changes.
*p*_total_ > 0.10	Safety	Differential MALE event rates between treatment groups could be causing higher event rate than anticipated.	Unblinded estimation of the MALE event rates in each treatment group.
(1) *δ*_Int_ = 0	Efficacy	*p*_exp_ = *p*_con_	Calculate Bayesian predictive probabilities for successful termination of trial. Continue the trial unless otherwise stated by DMB. Based on interim results, the DMB may suggest a sample size increase.
(2) *δ*_Int_ > 0	Efficacy: R1	MALE event rate in the experimental group is considerably higher than in the control group.	Quantification of “how much higher”. DMB discusses stopping for safety reasons.
(3) *δ*_Int_ < 0	Efficacy: R1	MALE event rate in the experimental group is considerably lower than in the control group.	Quantification of “how much lower”. DMB discusses stopping for safety reasons.

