**Table Tabc:** 

Continuous safety evaluation, after multiples of 150 patients at 12-month follow-up			
*d*_Int_ ≠ 0	Safety: R2	Unblinded estimation of mortality rates. Assess if mortality rates are different between treatment groups.	How much higher mortality rate in one group compared to the other after 12-month follow-up?

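### MALE is compared by arm at the interim only if the pooled rate exceeds 10%, so the trigger does not test the between-arm safety concern it serves and fails if control events run below plan

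*Protocol article*

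**What the plan says.** The section on monitoring for safety gives two concerns. The first, R1, is that "the efficacy endpoint (MALE) may differ substantially between treatment groups"; the second, R2, is that mortality may differ.

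Whether the arms are compared on MALE depends on the pooled rate. Under Interim analyses {21b}: "If at interim the overall event rate exceeds a pre-specified threshold of 10%, the event rate will be estimated in both treatment groups (unblinded". Statistical methods {20a} and the section on monitoring for efficacy repeat the condition. In the scenario table, a pooled rate at or below 10% is taken to mean that the nuisance-parameter assumptions look realistic, and the action is "Continue trial without any changes". Rows for a zero, positive or negative MALE difference apply only above 10%.

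A second table covers the safety evaluation at multiples of 150 patients. The only by-arm quantity it lists is mortality: "Unblinded estimation of mortality rates".

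The 10% threshold equals the planning rate in Sample size {14}: "assuming a 10% event rate (MALE) within 12 months in both the control and intervention group", with "a non-inferiority margin of 5% expressed as absolute risk difference".

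**The concern.** R1 concerns a difference between two rates; the trigger concerns their average. A higher rate in one arm and a lower rate in the other can leave the average at or below 10%. The plan would then record that its assumptions hold, and no MALE comparison by arm would follow.

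The events at stake are unplanned major amputation and target lesion re-vascularization for critical limb ischemia. The interim is the only point at which the article provides for comparing 12-month MALE between arms before the end of the trial. An excess larger than the trial's own 5-point margin could pass it unseen. The article fixes both the condition and the action, so this is a stated rule that does not serve its stated purpose, and not detail left to another document.

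**Working it through.** **Inputs.** Sample size {14}: 10% MALE in each arm, margin 5 points, one-sided 2.5%, 80% power, 566 per arm. Interim analyses {21b} and the scenario table: 300 per arm with 12 months of follow-up, arms opened if the pooled rate is above 10%. Control rates other than 10% are my assumptions, so a range is shown.

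**The plan's own figure.** n per arm = (1.960 + 0.842)² × (0.10 × 0.90 + 0.10 × 0.90) / 0.05² = 565.1, rounded up to 566, or 1132 in total. This reproduces "a total of 1132 patients (566 patients per treatment group".

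**The trigger in counts.** Above 10% of 600 means at least 61 events. The arms stay closed when X + Y ≤ 60, with X ~ Binomial(300, control rate) and Y ~ Binomial(300, control rate + excess), independent. The probabilities below are exact sums over the two distributions.

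| True control rate | Closed, 5-point excess | Closed, 6-point excess |
|---|---|---|
| 10% (planned) | 3.3% | 1.4% |
| 9% | 13.7% | 7.1% |
| 8% | 37.5% | 23.8% |
| 7% | 69.3% | 53.4% |
| 6% | 91.6% | 82.5% |
| 5% | 99.0% | 96.8% |

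The pattern is simple. The expected pooled rate is the control rate plus half the excess, and the arms are as likely closed as open when that sum is about 10.1%. The 50% point is therefore a control rate of about 7.6% for a 5-point excess (7.6 + 2.5 = 10.1) and 7.1% for a 6-point excess (7.1 + 3.0 = 10.1). Larger excesses need a lower control rate to be missed: about 5.1% for 10 points. At 5% vs 13% the arms stay closed 83% of the time.

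**No difference.** At 10% in both arms, P(X + Y ≤ 60) = 53.4%, so the arms are opened 46.6% of the time.

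**An observed split, with no assumed true rate.** Take 15/300 control and 45/300 sirolimus, or 5% vs 15%. Pooled: 60/600 = 10.0%, which does not exceed 10%. The difference is 10 points. SE = √(0.05 × 0.95/300 + 0.15 × 0.85/300) = 0.02415. The 95% interval is 10 ± 1.96 × 2.415, or 5.3 to 14.7 points, wholly beyond the 5-point margin. Even the 99.95% interval specified for the interim, 10 ± 3.48 × 2.415 or 1.6 to 18.4 points, excludes zero. A smaller split, 22/300 vs 38/300 (7.3% vs 12.7%), also totals 60 and stays closed.

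**How plausible is a low control rate?** Sample size {14} cites MALE rates from 1.5% at 12 months to 10% at 12 months, with 3.6% in previously re-vascularized patients (a study reported at 21 months) and 12.2% at 30 days in critical limb ischemia. It calls these sources heterogeneous. Rates below 7% lie within the cited range but are not the planning assumption.

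**The case against.** A reader might infer that an excess beyond the margin will usually be missed, or that the pooled rate says almost nothing about a difference. The documents do not support either. At the planned control rate, the chance of opening the arms rises from 47% with no excess to 97% with a 5-point excess. The rule is non-specific, but it is sensitive if the planning rate is right. Failure needs an excess in the sirolimus arm together with a control rate well below plan.

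Nor is limb harm invisible. The trial is open-label. Serious adverse events to 365 days and a 30-day composite of death and MALE are listed safety outcomes, and a major amputation would meet the serious-event definition. The DSMB reviews safety data at multiples of 150 patients and can recommend termination, and an events committee adjudicates events. These provisions stand as mitigation. None is stated as a by-arm comparison of 12-month MALE, so the gap narrows but does not close.

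The effect on enrolment is also limited. Treatment is a single procedure and the interim needs 600 patients with 12 months of follow-up. The trial status section gives 396 enrolled by 22 December 2021 and recruitment ending in Q4 2023. Assuming even accrual, 804 patients over about 21 to 24 months is 34 to 38 a month. By the time the 600th patient completes a year, about 1,000 to 1,060 of 1,200 would be randomized (600 plus 12 months' accrual), leaving some 140 to 200 still to be treated. That limits the consequence, but a board finding at this point would still matter to those patients.

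Finally, extra looks at the primary endpoint could affect type I error, since the plan spends alpha for one interim only. This is a fair constraint on the remedy.

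**Conclusion.** The concern holds in conditional form. The trigger cannot exclude the difference named as R1. If the control rate is at or near 10%, an excess at or just above the margin is rarely missed (1% to 3%). If it is below about 7.6% for a 5-point excess, or 7.1% for a 6-point excess, the comparison more likely than not never takes place, and the result is labelled as support for the design. The observed-count example shows that the rule can leave a 10-point excess unopened with its 95% interval entirely beyond the margin.

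These figures assume exactly 300 evaluable patients per arm, complete 12-month outcomes, independent binomial counts, and the literal reading that exactly 10.0% does not exceed the threshold. The DSMB charter and the full protocol are not shown and might add a by-arm MALE review; the article as published does not state one.

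**What to change.** In Interim analyses {21b}, Statistical methods {20a}, the section on monitoring for efficacy and the scenario table, remove the pooled-rate condition on the by-arm MALE estimate. State that the DSMB receives MALE counts by arm and the risk difference with its interval at the 600-patient interim whatever the pooled rate, for assessment of harm. State also that neither non-inferiority nor superiority may be declared from this look outside the existing alpha-spending plan. Keep the pooled rate only as a check of the sample-size assumption, and reword the first row of the table so that a pooled rate at or below 10% is no longer the sole ground for continuing unchanged.

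If by-arm MALE is also to be shown at the 150-patient reviews, the same harm-only restriction must be written for those looks.

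The cost is protocol and charter wording plus one more table for a board that already sees mortality by arm. Restricted to harm, the look adds no opportunity to claim non-inferiority or superiority. The downside is a possible false alarm: with 10% in both arms, an observed sirolimus excess above 5 points (at least 16 more events) arises by chance about 1.7% of the time. The board should therefore read the estimate with its interval.
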